## Abstract

The aim of this article is to present the research protocol for a prospective cohort study that will assess the olfactory function and the effect of an intervention based on olfactory training in healthy very old adults (≥75 years old). A convenience sample of 180 older people (50% female) will be recruited in three different environments: hospitalized control group (CH) with stable acute illness (*n* = 60); ambulatory control group (CA) of community-based living (*n* = 60); and an experimental odor training group (EOT) from nursing homes (*n* = 60). The odor training (OT) intervention will last 12 weeks. All the volunteers will be assessed at baseline; CA and EOT groups will also be assessed after 12 weeks. The primary end point will be change in olfactory capacity from baseline to 12 weeks period of intervention or control. The intervention effects will be assessed with the overall score achieved in Sniffin Sticks Test (SST) – Threshold, Discrimination, and Identification (TDI) extended version. Secondary end points will be changes in cognitive tasks, quality of life, mood, immune status, and functional capacity. All these measurements will be complemented with an immune fitness characterization and a deep proteome profiling of the olfactory epithelium (OE) cultured *ex vivo*. The current study will provide additional evidence to support the implementation of olfactory precision medicine and the development of immunomodulatory nasal therapies based on non-invasive procedures. The proposed intervention will also intend to increase the knowledge about the olfactory function in very elderly people, improve function and quality of life, and promote the recovery of the health.

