## Introduction

Europe is aging. In 2050, more than 28% of the population will be over the age of 65 (United Nations, 2019). The continuous declining of birth rates and the increasing of life expectancy are converting European regions into increasingly aging area. Neurodegenerative diseases (ND) are a significant portion of neurological disorders and these already account for 1/3 of the cost of illness in Europe furthermore social and economic burden will continue to increase as the population ages (Deuschl et al., 2020). Addressing the human and economic challenge of aging and neurodegenerative diseases requires clinical and research tools that facilitate precision medicine. We need disruptive approaches that generate innovative tools for early detection and diagnosis of ND and non-invasive interventions to slow and/or stop its progression in women and men, highlighting their differences if any, and incorporating a gender perspective in the solutions.

The olfactory function is responsible for detecting and processing odors, and is one of the oldest and most important senses for living organisms (Delgado-Losada et al., 2020). The sense of smell provides important information about the air we breathe, the foods we eat and alert us to dangers in the environment (Schiffman, 1997; Hadley et al., 2004; Schriever et al., 2014). Beyond the risks that the smell loss may entail for older people, moreover the consequent reduction in quality of life, the olfactory dysfunction may be an important early indicator of ND such as Parkinson’s and Alzheimer’s (Djordjevic et al., 2008; Haehner et al., 2013; Knudsen et al., 2015; Doty, 2017; Marin et al., 2018; Kondo et al., 2020), as well as COVID-19 (Moein et al., 2020; Sedaghat et al., 2020). In addition, olfactory system dysfunctions have been found in other neurological disorders such us schizophrenia, or depression (Sanna et al., 2021) ultimately related to alterations of the immune system, suggesting that olfactory system abnormalities may be also associated with the immune system (reviewed in Strous and Shoenfeld, 2006). During the last years, olfactory proteomics has been postulated as a powerful approach to characterize global proteome dynamics in order to unravel the modulation of cell-signaling networks during odor processing (Lachén-Montes et al., 2016), as well as during the neurodegenerative process (Lachén-Montes et al., 2017, 2019a,b, 2020a).

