In the literature, there is a full consensus stating that sense of smell gradually decreases with age, especially after the age of 60 (Doty et al., 1984; Murphy et al., 2002; Doty et al., 2011; Mullol et al., 2012; Hummel, 2014; Sorokowska et al., 2015; Masala et al., 2018; Doty, 2019; Kondo et al., 2020). In relation to sex differences, by one side Doty et al. (1984) have observed that women outperformed men at all ages in healthy subjects, and a recent meta-analysis has confirmed the female olfactory superiority, although authors emphasized the effect sizes observed were notably small (Sorokowski et al., 2019). By other side, when comparing healthy control subjects with Parkinson’s disease patients, new findings (Melis et al., 2019; Solla et al., 2020) have remarked the importance of sex effect analysis. Regarding smoking, there is no consensus indicating that it accelerates olfactory dysfunction (Vennemann et al., 2008; Fjaeldstad et al., 2021). However, there is evidence that current smoking, but not former smoking, was associated with posttraumatic olfactory loss; namely, a history of smoking was not associated to impairment of olfactory function (Vennemann et al., 2008). Related to lifestyle and behavior factors, the regular exercise was associated with a lower 10-year cumulative incidence of olfactory impairment; in addition, the association with exercise was more robust among those who exercised three or more times per week than among those who only exercised 1–2 times per week (Schubert et al., 2013).

Training and repeated exposure to odorants leads to enhanced olfactory sensitivity (Al Aïn et al., 2019). The olfactory or odor training (OT) is a non-invasive technique with no significant side effects. Previous studies have proven the usefulness of OT in handling olfactory deficits with various etiologies (Hummel et al., 2009; Patel, 2016; Pekala et al., 2016; Al Aïn et al., 2019). The OT may be considered a simple protocol, which has proven efficacy in some patients with olfactory dysfunction. Despite increasing acceptance as an appropriate intervention, questions related to both efficacy and mechanism of action have persisted (Hummel et al., 2009; Turner, 2020).

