Although there are important findings showing that intensive OT can improve olfactory function and in addition, this improvement is associated with changes in the structure of olfactory processing areas of the brain (Al Aïn et al., 2019). More research is needed to establish the optimal protocols i.e., quantity of odorants, training duration, associated-molecular events, and the target patient population most likely to improve using this technique (Patel, 2016). Therefore, the aim of this pilot study is to examine the effects of a well-controlled and semi supervised 12-weeks OT on olfactory function, OT-associated OE proteostatic changes, cognitive, immune and functional status, and quality of life in very elderly adults.

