## Materials and Methods

### Study Design and Participants

The sample is a convenience sample and is composed by three groups (*N* = 180, 50% females). Sixty hospitalized patients with acute illness (hospitalized control group – CH), sixty ambulatory patients from the community (ambulatory control group – CA) and, sixty from nursing home – the experimental odor training group (EOT). The study follow the principles of the Declaration of Helsinki (World Medical Association, 2013) and was approved by the Complejo Hospitalario de Navarra Clinical Research Ethics Committee on October 21, 2020 (PI_2020/113). All volunteers or their legal representatives will be asked to sign a written informed consent form, also approved in advance by the ethics committee. There will be no financial compensation.

Following the literature procedures (Delgado-Losada et al., 2020) all the volunteers will be previously evaluated by an expert otolaryngologist including anamnesis and nasal endoscopic examination to exclude the possibility of an otorhinolaryngology alteration or pathology that may modify the results of the olfactory test. Therefore, sinusitis, prior nasal surgery, nasal polyps, presence of nasal congestion at the moment of test administration or recent upper respiratory tract infection within two weeks, medication intake with repercussion in olfactory performance or to have reported COVID-19 compatible smell symptomatology are exclusion criteria.

The inclusion criteria are: (i) ≥ 75 years old; (ii) compliance with testing procedure; (iii) Mini-Mental State Examination (MMSE) equal to or greater than 21 points (Pi et al., 1994; Ostrosky-Solís et al., 2000; Reyes-de-Beaman et al., 2004); (iv) Barthel index ≥ 60; (v) participants from acute hospitalized group must be clinically stable. The exclusion criteria are positive diagnosis of any kind of neurodegenerative disease and/or nasosinusal pathology (described before).

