### Data Analysis

Demographic and outcome data will be summarized for the whole sample and for each group using mean and standard deviation or median and interquartile range for continuous variables and via frequencies and percentages for categorical ones. For the CH group only a descriptive characterization of the measured variables will be performed. In the CA and EOT groups, baseline data will be compared using t-test or Mann-Whitney U test for continuous variables and with chi-square test and Fisher test for categorical ones. For each group, within group pre-post differences will be computed using t-test for dependent samples or Wilcoxon rank sum test. Linear models will be computed in order to compare outcome data between groups, adjusting by baseline outcome data and also by the variables that showed baseline differences.

Further, the association between olfactory level measured with TDI score and marked OE protein modifications (based on fold-change), cognitive, neurological, functional, mood status and quality of life will be analyzed using Pearson or Spearman correlation coefficients. All significant, nearly significant, clinically relevant or potentially confounding variables will be considered in a multiple linear regression model with TDI as dependent variable. In this global model non-significant variables will be removed, which, when eliminated, do not change the estimators of the effect of the rest of the variables in the model. The biochemical analysis, the immune information of each subject and the data associated with pharmacological treatments, fragility, cognition, will also be correlated with olfactory level, with the aim of testing the precision olfactory medicine as a useful tool in the day-to-day context of the Geriatrics Unit. To exclude the effect of sex and age, correlations will be performed as partial correlations, including sex and age as covariates. The statistical analysis will be performed with SPSS (version 26; SPSS Inc., Chicago, IL, United States).

Sample size was calculated based on previous literature (Hummel et al., 2009) on the effects of OT on olfactory function, a medium effect size (*d* = 0.5) and a standard deviation of the outcome of *SD* = 0.8 were assumed (Birte-Antina et al., 2018).

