### Intervention

#### Control

The control group will be composed by sixty ambulatory patients from the community (CA). This group will undergo a complete assessment at baseline and after 12 weeks. The volunteers of CA group will receive usual health care assistance; therefore they will not participate in any kind of olfactory training.

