#### Training Protocol

The experimental odor training group (EOT) will be composed by sixty older adults from nursing home. This group will undergo a complete assessment at baseline and after 12 weeks. The training intervention will be performed over a period of 12 weeks and will involve patients exposing themselves once daily to 4 different scents of the four commonly used odors during 20 s each (phenyl ethyl alcohol (PEA): rose, eucalyptol: eucalyptus, citronellal: lemon, and eugenol: cloves). These four odorants were chosen to be representative of four odor categories that tried to identify/represent primary odors (Amoore, 1977; Haehner et al., 2013). These categories are flowery (e.g., rose), foul, fruity (e.g., lemon), aromatic (e.g., cloves), burnt, and resinous (e.g., eucalyptus). Training patients received four vial topaz (total volume 5 ml) with one of the four odors in each (1 ml each, soaked in cotton pads to prevent spilling). All vials will be labeled with the odor name. Patients will be asked to sniff the odors in the morning for approximately 20 s each. Participants will be asked to refrain from smoking, eating, or drinking (except water) during the hour prior to training and testing (Al Aïn et al., 2019). Figure 2 shows a summary outline of the proposed protocol.

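### The 50% female target is set only for all 180, and sex enters the EOT–CA model only if it differs at baseline, so the two compared groups may differ in sex mix without adjustment

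*Protocol article*

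**What the plan says.** **Rationale.** The Introduction calls for work on neurodegenerative disease "in women and men, highlighting their differences if any, and incorporating a gender perspective in the solutions". It later reviews sex differences in smell and says that recent findings "have remarked the importance of sex effect analysis".

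**Sample.** The Abstract states: "A convenience sample of 180 older people (50% female) will be recruited in three different environments". Study Design and Participants repeats that the sample "is composed by three groups (*N* = 180, 50% females". Neither place says that the 50% holds within each group.

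**Groups compared.** In Training Protocol: "The experimental odor training group (EOT) will be composed by sixty older adults from nursing home". In Control: "The control group will be composed by sixty ambulatory patients from the community (CA". Participants are not randomised; group follows the setting from which they are recruited.

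**Analysis.** Under Data Analysis, CH is only described. CA and EOT are compared at baseline with significance tests. The linear models for outcome then adjust for baseline outcome and for the variables found to differ. Sex is named in one sentence, which concerns the correlations of TDI with other variables: "To exclude the effect of sex and age, correlations will be performed as partial correlations, including sex and age as covariates". No EOT–CA estimate by sex is specified.

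**The concern.** Two stated rules combine badly. The 50% target covers a total that includes 60 people who take no part in the EOT–CA comparison, so CH can absorb any imbalance between the two groups that matter. Adjustment for sex then depends on a baseline test, which with 60 per group can miss a sizeable difference. The article itself reports that sex is related to smell, so sex is a known prognostic factor whose place in the model should not depend on a test result.

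Drift is plausible. The two training studies in older people listed in Table 1 had 78% and 70% women, and EOT and CA are convenience samples from different settings.

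Two things are at stake. The EOT–CA difference in TDI could carry some effect of sex mix. And although the rationale raises sex differences, the article specifies no estimate of the EOT–CA difference for women and for men.

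**Working it through.** **1. Can the target be met with EOT and CA unbalanced?**

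Inputs: 60 per group and 50% of 180 = 90 women (Study Design and Participants). Illustrative split: 40 women in EOT, 30 in CA, 20 in CH.

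- Total: 40 + 30 + 20 = 90, so the target is met exactly.
- EOT 40/60 = 67%, CA 30/60 = 50%, a difference of 17 percentage points.

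**2. Would the baseline test bring sex into the model?**

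The article gives no threshold for a baseline difference; p < 0.05 is assumed here. For the 2×2 table with rows 40/20 and 30/30:

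- Chi-square = N(ad − bc)² / (product of margins) = 120 × (40×30 − 20×30)² / (60×60×70×50) = 120 × 360,000 / 12,600,000 = 3.43.
- Uncorrected p is about 0.06.

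So sex would not be adjusted for. With one more woman in EOT (41 against 30), chi-square = 120 × (41×30 − 19×30)² / (60×60×71×49) = 4.17, p about 0.04, and sex would enter. The model would change on one participant.

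**3. How large could the bias be?**

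Unadjusted bias = (difference in proportion of women) × (sex difference in the outcome that remains after baseline adjustment). With step 1 this is 1/6 of that remaining difference. If the remaining difference were as large as the d = 0.5 that the article assumes for training, the bias would be 0.5 / 6 = 0.08 SD. The Introduction describes the sex effect as small, and adjustment for baseline TDI removes much of any stable difference, so the realistic figure is lower.

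**4. What precision would an estimate by sex have?**

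Assumptions: 30 women and 30 men in each of EOT and CA, no dropout, two-sided 5%, common SD, t multiplier about 1.98.

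| Quantity | SE (SD units) | 95% CI half-width |
|---|---|---|
| EOT–CA, both sexes | √(2/60) = 0.183 | 0.36 |
| EOT–CA within one sex | √(2/30) = 0.258 | 0.51 |
| Difference between the sexes | √(4/30) = 0.365 | 0.72 |

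Baseline adjustment multiplies these by √(1 − r²), where r is the correlation of baseline with final TDI. The article does not give r. For an assumed r of 0.6 to 0.7, the last half-width becomes 0.72 × 0.80 = 0.58 to 0.72 × 0.714 = 0.52 SD.

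The sex difference detectable with 80% power is (1.96 + 0.84) × 0.365 = 1.02 SD without baseline adjustment, or 0.73 SD at r = 0.7. Power for a sex difference of 0.5 SD is about 28%, rising to about 48% at r = 0.7.

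**The case against.** The other side has a strong case, and much of it stands.

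- **A reader might infer that sex differences are an objective left unanswered.** They are not. The Introduction sentence states what the field needs, and the remark on sex effect analysis concerns comparisons of Parkinson's patients with healthy controls. The stated aim is that "the aim of this pilot study is to examine the effects of a well-controlled and semi supervised 12-weeks OT on olfactory function", and neither the outcomes nor the expected results name a sex comparison.
- **A reader might infer that sex is only partialled out.** The partial-correlation sentence does not govern the training model. Sex can enter the EOT–CA model if it differs at baseline, and the separate TDI regression as a clinically relevant or confounding variable.
- **A reader might infer that the trial cannot answer the question.** Sex is recorded, so an estimate by sex can be made from data already planned. What is limited is precision.
- **Exploratory interactions are commonly left to a full protocol or SAP.** This is correct: the absence of a group-by-sex term from a condensed article would not be a point by itself.
- **The power is poor, and setting confounds the contrast.** Also correct. It restricts how an estimate by sex may be labelled and read.
- **The wording leaves open whether 50% also holds within groups.** It may be so intended. If it is, saying so costs nothing.

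What these objections do not remove is the combination of two rules that the article does state: a target set for the total, and adjustment that depends on a baseline test. The possible route for sex into the EOT–CA model fails in exactly the case worked through above.

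**Conclusion.** The point holds as a minor one. As written, EOT and CA can differ by 17 percentage points in the proportion of women while the 50% target is met exactly and sex stays out of the model. This assumes a 0.05 threshold for a baseline difference and an uncorrected chi-square test. The resulting bias is one sixth of whatever sex difference remains after baseline adjustment: at most about 0.08 SD if that difference were 0.5 SD, and probably less.

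The article also raises sex differences in its rationale without specifying an EOT–CA estimate by sex. Such an estimate is available, but only with a 95% CI of about ±0.51 SD within one sex and ±0.72 SD for the difference between the sexes, before baseline adjustment and without dropout. It would describe, not test. The documents do not support saying that the trial leaves one of its objectives unanswered or is unable to address sex.

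**What to change.** 1. **Recruitment.** State that the 50% target applies within EOT and within CA, that is, 30 women and 30 men in each. The downside is that men may be slower to recruit in nursing homes.
2. **Main model.** Include sex as a fixed covariate in the EOT–CA model for TDI, whatever the baseline test shows. This costs one parameter in a comparison of 120 people.
3. **Exploratory addition.** Fit one further model with a group-by-sex term and report the EOT–CA difference for women and for men, and the difference between them, each with a 95% CI. Label it exploratory. State the expected half-width for the sex difference (about ±0.72 SD, less with baseline adjustment), that it is not a powered test, and that each contrast mixes training with setting (nursing home against community), so neither should be called the training effect in that sex.

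No new visits, measurements or participants are needed. Fixing these rules before the data are seen is also better than splitting by sex after the results are known.

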### Intervention

#### Control

The control group will be composed by sixty ambulatory patients from the community (CA). This group will undergo a complete assessment at baseline and after 12 weeks. The volunteers of CA group will receive usual health care assistance; therefore they will not participate in any kind of olfactory training.

#### Training Protocol

The experimental odor training group (EOT) will be composed by sixty older adults from nursing home. This group will undergo a complete assessment at baseline and after 12 weeks. The training intervention will be performed over a period of 12 weeks and will involve patients exposing themselves once daily to 4 different scents of the four commonly used odors during 20 s each (phenyl ethyl alcohol (PEA): rose, eucalyptol: eucalyptus, citronellal: lemon, and eugenol: cloves). These four odorants were chosen to be representative of four odor categories that tried to identify/represent primary odors (Amoore, 1977; Haehner et al., 2013). These categories are flowery (e.g., rose), foul, fruity (e.g., lemon), aromatic (e.g., cloves), burnt, and resinous (e.g., eucalyptus). Training patients received four vial topaz (total volume 5 ml) with one of the four odors in each (1 ml each, soaked in cotton pads to prevent spilling). All vials will be labeled with the odor name. Patients will be asked to sniff the odors in the morning for approximately 20 s each. Participants will be asked to refrain from smoking, eating, or drinking (except water) during the hour prior to training and testing (Al Aïn et al., 2019). Figure 2 shows a summary outline of the proposed protocol.

**FIGURE 2 F2:**
[figure not shown]
Odor training protocol (own elaboration).

Adherence to the OT intervention will be documented in an *Odor training diary* (P.R.O-V1.1E, 2020). By one side, some protocols in literature (Table 1) performed the training sessions twice a day or 12 weeks of OT (Hummel et al., 2009; Haehner et al., 2013; Schriever et al., 2014; Fornazieri et al., 2019). However, by other side, Schriever et al. (2014) and Fornazieri et al. (2019) have indicated that only half part of the sample strictly follow the protocol. In this regard, our main objective is to propose a protocol that can be followed in an easy and manageable way by our sample of very old adults. For this reason, we propose only one training session per day during a 12 weeks period. In the same way, seems important to highlight that at least once a week a researcher of our staff will supervise the training sessions and furthermore participants will receive a follow up call per week. Lastly, participants who do not experience a subjective perceived improvement in olfactory function tend to lose motivation, so there will be an intermediate smell test with SST at 6 weeks to assess objectively the evolution of performance.

